### Secondary outcomes

Treatment acceptability and feasibility (Aim 2) will be determined by the quantitative and qualitative data obtained from online surveys and semi-structured interviews with the young person, family members and therapist. A range of health economic assessments will also be conducted, including quantifying the resources used (costs) and consequences associated with FBT telemedicine or standard care (face-to-face) from a societal perspective; longitudinally examining the impact of socioeconomic, demographic and illness factors on health-related quality of life; and assessing inequalities in access to healthcare for young people with AN during the study (Aim 3).

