**Method:**

Forty young people aged 12 to 18 years who meet DSM-5 diagnostic criteria for AN, and live in a rural or regional setting, will along with their family be recruited to the study. Trained therapists will provide 18 sessions of FBT over 9 months via telemedicine to the home of the young person and their family. The analysis will examine treatment effectiveness, feasibility, acceptability, and cost-effectiveness.

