## Method

### Overall study design

This is a four-year pre- and post-implementation study, with 2 years dedicated to treatment delivery, and up to 20 families per year, to reach a total sample size of 40 families. The study commenced in April 2020 (see Fig. 1 for the Study Timeline). The study protocol has been approved by a Human Research Ethics Review Board (HREC #2020/ETH00186).

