#### Aim 3: Health economic assessments

The health economic assessments will consist of three analyses. Firstly, a costs (resources used) and consequences (health outcomes) analysis in which all the direct (medical) costs, indirect costs (e.g. proportion of total internet usage, parents’ time off work to engage in the intervention) and a catalogue of health outcomes (including clinical and health-related quality of life measures) between T1 and T3, and T1 and T4 will be quantified and reported. A societal perspective will be adopted for this analysis, enabling consideration of costs and consequences related to the young person with AN, their family members/carers and the therapist. A resource use database will be developed to collect information on type, amount and value (in dollars) of the healthcare resources associated with the FBT intervention via telemedicine or standard care (face-to-face mode), including the cost of staff training, time costs of the therapist to deliver FBT, laboratory costs, hospitalisations, GP visits, specialist visits, allied health other than through the study, and prescribed treatments and medications. In addition, out-of-pocket costs such as time cost of internet in the home and time off work for parents to engage in the intervention will be collected. This resource use data will be collected using detailed cost questionnaires administered at baseline (T1), T2, T3 and follow-up (T4).

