This study will provide quantitative data regarding the effectiveness of FBT via telemedicine on eating disorder and other relevant outcomes. However, the study will also provide important qualitative insights into the experiences of delivering and receiving treatment for AN via telemedicine during an unprecedented time. The interviews will explore the technical, ethical, and practical issues of delivering therapy via telemedicine, both in general and also when working with more than one client (i.e., with families). Further, the interviews will be able to capture the complexity of the family’s experience receiving FBT [43, 61, 69]. Further, the health economic assessments will involve (1) identifying, measuring and valuing both the costs and the consequences of FBT telemedicine or standard care (face-to-face); (2) assessing how changes in health-related quality of life are associated with demographic, socioeconomic and illness-related measures; and (3) an assessment of changes in inequalities in access to healthcare over time for young people with AN. The health services change required to meet the needs of regional and rural populations must not only be effective in reducing core eating disorder symptomology but also acceptable and cost-effective.

To begin with, we are focusing recruitment on regional and rural locations, as there has always been an increased need for telemedicine in these areas [24, 25], which is anticipated to increase over the next 2 years due to COVID-19 [14, 30, 31, 34, 39, 40, 70]. Should the study demonstrate that telemedicine is effective, acceptable and feasible for this geographical group, then clinicians can consider the modality as a viable method to effectively disseminate treatment to families not able to attend face-to-face sessions for a multitude of reasons. The COVID-19 pandemic forced therapists and families to rapidly adjust to online modes of treatment delivery. This may help telemedicine establish a more permanent place within health service frameworks and service delivery models. However, further understanding of the differences between online and face-to-face treatment is required to ensure that telemedicine is safe, effective and that young people diagnosed with AN can access evidence-based care, irrespective of their location.

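### The plan promises costs and consequences of face-to-face standard care, and cost-effectiveness, but every family receives telemedicine and no face-to-face source is described

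*Protocol article*

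**What the plan says.** **Design.** Overall study design states: "This is a four-year pre- and post-implementation study, with 2 years dedicated to treatment delivery", with "up to 20 families per year, to reach a total sample size of 40 families". The abstract says: "Trained therapists will provide 18 sessions of FBT over 9 months via telemedicine to the home of the young person and their family". The Intervention section describes the same single mode of delivery for everyone.

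**Economic aim.** Under Specific aims, the third aim concerns the costs and health consequences of delivering FBT by telemedicine. It names no comparator.

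**Economic outcomes and analysis.** Secondary outcomes goes further: "quantifying the resources used (costs) and consequences associated with FBT telemedicine or standard care (face-to-face) from a societal perspective". Aim 3 under Data analysis plans a database of "healthcare resources associated with the FBT intervention via telemedicine or standard care (face-to-face mode"). The Health economics section and the Discussion pair telemedicine with face-to-face standard care in the same way. The abstract's Method paragraph says: "The analysis will examine treatment effectiveness, feasibility, acceptability, and cost-effectiveness". The abstract's Discussion paragraph makes its conclusion depend on the treatment proving economically as well as clinically effective.

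**Data source.** Health economics and Aim 3 both name cost questionnaires at T1, T2, T3 and T4. Table 1 assigns the cost items to the young people with AN and their families, and its one delivery-cost row concerns the telemedicine intervention.

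**Effectiveness.** Primary outcomes and Aim 1 use change from T1 to T3 and from T1 to T4, together with a remission threshold of more than 85 %mBMI.

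**The concern.** A stated secondary outcome needs data on face-to-face care, and the design described supplies none. The article gives the design, the assessment schedule and the data source explicitly, so this is a conflict within its own text and not a detail lost in condensing it.

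A cost-effectiveness statement compares two courses of action. The Background frames the evidence gap in those terms, as the lack of evidence on telemedicine FBT against face-to-face care. If the wording stays, the final report must either leave a declared outcome unreported or fill the comparator from a source chosen after the results are known.

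Aim 1 raises a related issue. Young people enter the study ill, and their general practitioner or psychiatrist manages their medical and psychiatric health in parallel. Improvement from T1 therefore mixes any treatment effect with natural course, regression to the mean and co-management.

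**Working it through.** **1. The plan's own figure.** 2 treatment years × up to 20 families per year = 40 families. This reproduces the stated total.

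**2. Who supplies which data.**
- Families treated by telemedicine: 40.
- Families treated face-to-face within the study: 40 − 40 = 0.
- Historical or pre-implementation cohort: none described. The phrase "This is a four-year pre- and post-implementation study" could suggest one, but T1 to T4 are time points in the same treated families.
- External source: Health economics mentions published data, but for unit costs. Those are prices. They give neither the quantities used in a face-to-face FBT course nor its outcomes.
- Resource use at T1: this records earlier care of the same families. Being in other psychological or dietetic care for AN excludes a family at entry.

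**3. What can be computed.** An incremental analysis needs

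ΔC = C(telemedicine) − C(face-to-face) and ΔE = E(telemedicine) − E(face-to-face),

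and a cost-effectiveness ratio is ΔC/ΔE. The study supplies the first term of each difference. Nothing described supplies the second, so ΔC, ΔE and their ratio are undefined from study data. A list of costs and consequences under telemedicine can be computed in full.

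**4. Precision of the Aim 1 remission proportion.** The Background cites about 40% remission at the end of FBT. As an illustration, suppose the same share remits here: 0.40 × 40 = 16 of 40.
- Exact (Clopper-Pearson) limits: the 2.5% point of Beta(16, 25) and the 97.5% point of Beta(17, 24), which are 24.9% and 56.7%.
- Wilson interval: 26.3% to 55.4%.

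The exact interval is 56.7 − 24.9 = 31.8 points wide.

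**5. Would a face-to-face arm within 40 families repair this?** The article gives no alpha, power or margin, so these inputs are assumptions: 40% remission in both modes, one-sided alpha 0.025, 80% power. Then n per arm = (1.960 + 0.842)² × (0.24 + 0.24) / margin².

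| Margin (points) | n per arm |
|---|---|
| 10 | 377 |
| 15 | 168 |
| 20 | 95 |

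Splitting the 40 families 20/20 gives about 24% power to detect 40% against 60% (two-sided 0.05). A second arm at this size would not support a firm comparison, so the realistic repair lies in the wording or in a named external source.

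**The case against.** The strongest reply is that the study's real economic plan is modest. Aim 3 under Specific aims is not comparative. The analysis section specifies a listing of costs and consequences, with no ratio, incremental estimate or threshold, and the Discussion speaks of preliminary health-economic estimates. As a planned analysis of this study, cost-effectiveness appears only in the abstract. This is right, and it is why the repair is small. It does not remove the conflict, because four sections still name face-to-face standard care as something to be costed.

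A second reply is that the source of a modelled standard-care costing could sit in a fuller protocol or health-economic plan. That would be fair if the article were silent. It is not: it names participants' questionnaires as the source.

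Three stronger readings are tempting, and the documents do not support them.

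- **That no face-to-face care is captured at all.** The questionnaires cover GP and specialist contacts, hospital stays and allied health outside the study. Previous treatment is recorded, and so is continuing treatment after T3. What is missing is a face-to-face FBT course with its outcomes.
- **That the study claims equivalence with face-to-face FBT.** The statement of equal effectiveness in the Discussion describes the earlier USA pilot, and its limits are given there. This study sets no equivalence or non-inferiority hypothesis. The sentence beginning "Should the study demonstrate that telemedicine is effective, acceptable and feasible for this geographical group" makes no comparison with face-to-face care, and the same section says the differences between the modes need further study.
- **That effectiveness rests only on change from baseline.** Primary outcomes also uses an absolute weight threshold, and the Measures section defines full remission by that threshold plus an EDE criterion.

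**Conclusion.** The point holds for the economic comparison. As written, the costs and consequences of face-to-face standard care, and the cost-effectiveness promised in the abstract, cannot be delivered from the design described. This rests on reading the text and on no assumed figure: zero of 40 families provide a face-to-face FBT course, and no external source of its quantities and outcomes is named.

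For Aim 1 the point is narrower. The study can estimate change and remission proportions under telemedicine FBT. It cannot attribute them to telemedicine or show parity with face-to-face delivery. The interval of 25% to 57% assumes 16 remissions among 40 families with complete data; it illustrates precision and does not forecast the result. Any comparison with the roughly 40% in the Background is descriptive only, because the article does not give the remission definition behind that figure. A reader might infer that the plan must test against 40%; the documents give no basis for requiring that.

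The single-arm design is openly declared and is not itself the error. The correction is needed because it changes what the study can conclude.

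**What to change.** 1. Delete the face-to-face standard-care alternative from Health economics, Secondary outcomes, Aim 3 under Data analysis, and the Discussion. The text then matches Aim 3 under Specific aims.
2. In the abstract's Method paragraph, replace cost-effectiveness with a single-arm cost-consequence description. In the abstract's Discussion paragraph, reword the condition about economic effectiveness to match.
3. If a comparison is wanted instead of steps 1 and 2, name the external source of face-to-face quantities and outcomes, and label the result as indirect or modelled.
4. Under Aim 1, state that the study estimates uncontrolled change and remission proportions, and report the proportions with exact 95% CIs. State that these are not attributed to telemedicine and do not show parity with face-to-face FBT. Mark any mention of the 40% figure as descriptive.

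Steps 1, 2 and 4 change wording only and need no new data collection. Step 3 would require finding and justifying the source. The price of the wording route is more modest conclusions.

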### Data analysis

#### Aim 1: Effectiveness of delivering FBT via telemedicine

A mixed model logistic regression will be used to evaluate the effectiveness of FBT delivered via telemedicine, using change of %mBMI as the primary outcome from T1 to T3 and from T1 to T4. To determine the effectiveness, secondary analyses, again using a mixed model regression, will compare the young persons’ global EDE and EDE-Q, as well as the parents/guardians PEDE and PEDE-Q scores. Further, the young persons’ responses on the CIA, CET at T1, T2, T3 and T4 will be compared. The young persons’, parent/guardians, and sibling/other family members responses on the FAD and EQ-5D-5L/EQ-5D-Y in addition to the parent/guardian responses on the PVA will be analysed to determine changes in family functioning, parental efficacy, and wellbeing from T1 to T3 and T1 to T4.

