### Measures

Psychometric questionnaires will be utilised throughout treatment for research purposes and to monitor treatment progress. There will be several assessment points: baseline (T1), throughout treatment, mid-treatment (T2), end-of-treatment (T3), and at 6 months follow-up (T4) (see Table 1 for assessment schedule). In addition to psychometric questionnaires, the young person, parents/guardians and therapist will be invited to participate in a semi-structured interview at T3. The young person, parents/guardians, siblings/other family members and therapist will complete the assessments via a secure online data capture portal, REDCap. REDCap is a secure web application for building and managing online surveys and databases which is licenced to the University of Sydney. REDCap is compliant with just about any privacy and security standard – for example, HIPAA, Part-11, and FISMA standards (low, moderate, or high).

**Table 1 Tab1:** Assessment Battery and Schedule

	Baseline (T1)	Weekly (until T3)	Mid-Treatment (Session 9 (T2)	End of treatment (Session 18) (T3)	6-month Follow-up (T4)
*Demographics: age, gender, education, location etc*	X				
*Illness characteristics: duration, symptoms*	X				
*Wait time to commence FBT*	X				
*Resource use in HE: Hospital admissions (number and duration)*	X		X	X	X

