**Young Person**					
*Weight (% mBMI)*	X	X	X	X	X
*Eating Disorder Examination (EDE)*	X		X	X	X
*Eating Disorder Examination – Questionnaire (EDE-Q)*	X		X	X	X
*Clinical Impact Assessment (CIA)*	X		X	X	X
*Compulsive Exercise Test (CET)*	X			X	X
*Family Assessment Device (FAD)*	X		X	X	X
*Revised Children’s Anxiety and Depression Scale (RCADS)*	X		X	X	X
*Rosenberg Self Esteem Scale*	X		X	X	X
*EQ-5D-5L* or *EQ-5D-Y*	X		X	X	X
*Ongoing treatment post T3*					X
*Evaluation of treatment*				X	

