**Parents/Guardians**					
*Family Assessment Device (FAD)*	X		X	X	X
*Parents* Versus *Anorexia Scale (PVA)*	X	2, 4, 6	X	X	
*Parent Eating Disorder Examination (PEDE)*	X		X	X	X
*Parent Eating Disorder Examination – Questionnaire (PEDE-Q)*	X		X	X	X
*Revised Children’s Anxiety and Depression Scale (RCADS) - Parent*	X		X	X	X
*EQ-5D-5L*	X		X	X	X
*Evaluation of treatment*				X	

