### Primary outcomes

To determine treatment effectiveness (Aim 1), an increase in %mBMI to greater than 85% will be used as an indicator of remission from pre-treatment (T1) to post-treatment (T3) and pre-treatment (T1) to six-month follow-up (T4). In addition, changes from T1 to T3 and T1 to T4 in eating disorder symptomology (global score on the EDE/EDE-Q and PEDE/PEDE-Q), exercise behaviours (CET) and impairment (CIA); general mental health (RCADS and RCADS-P); quality of life (EQ-5D-5L and EQ-5D-5L-Y); family functioning (FAD); and, parental self-efficacy (PVA).

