#### Aim 2: To determine the feasibility and acceptability of using telemedicine to deliver FBT

To examine the feasibility and acceptability of using telemedicine to deliver FBT we will utilise a mixed-method approach to analyse: (a) the number of patients/families that expressed interest in participating in the study; (b) the number of patients/families enrolled in the study (i.e., an indicator of treatment feasibility); (c) the number and percent of patients/families that completed at least 10 sessions (i.e., an indicator of treatment engagement); (d) the number of patients/families completing the full course of treatment (18 sessions; i.e., an indicator of treatment retention); (e) the results from the post-treatment evaluation survey and semi-structured interview by family members (i.e., family acceptability); (f) the results from the post-treatment evaluation survey and semi-structured interview by young people (i.e., young person acceptability); and (g) the results from the post-treatment evaluation survey and semi-structured interview by therapists (i.e., therapist acceptability).

A qualitative analysis will examine the participants’ responses to the semi-structured interviews that take place at T3. Given the lack of theory or framework regarding family acceptability and feasibility using telemedicine, a conventional content analysis method will be used [65]. The interviews will be analysed within and between participant roles (i.e., young persons, parents/guardians, siblings/other members and therapists) to determine what themes emerge that are similar across the groups, as well as those unique to each group. Two investigators (AH and [name]) with experience in qualitative research will immerse themselves in the data and allow for categories and names for categories to emerge from the data.

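### Table 1 schedules no PVA at six-month follow-up although PVA change from T1 to T4 is a planned outcome; CET at T2 and sibling interviews need the same reconciliation

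*Protocol article*

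**What the plan says.** Measures sets the assessment points: "baseline (T1), throughout treatment, mid-treatment (T2), end-of-treatment (T3), and at 6 months follow-up (T4"). Table 1 gives each instrument a row across five columns: T1, weekly until T3, T2, T3 and T4.

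**PVA.** Primary outcomes lists changes from T1 to T3 and from T1 to T4 in a series of measures that ends with "family functioning (FAD); and, parental self-efficacy (PVA"). Data analysis, Aim 1 repeats both intervals for the parents' PVA responses. In the Parents/Guardians block of Table 1, PVA is scheduled at T1, at points 2, 4 and 6 in the weekly column, at T2 and at T3. The T4 cell is empty.

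**CET.** Data analysis, Aim 1 says the young persons' "responses on the CIA, CET at T1, T2, T3 and T4 will be compared". In the Young Person block of Table 1, CET is marked at T1, T3 and T4 only.

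**Sibling interviews.** Data analysis, Aim 2 says: "The interviews will be analysed within and between participant roles (i.e., young persons, parents/guardians, siblings/other members and therapists"). Under Measures, the young person, "parents/guardians and therapist will be invited to participate in a semi-structured interview at T3"; siblings are not in that list. The Siblings/other family members section describes only a short online survey as their treatment evaluation. Secondary outcomes and item (e) of Aim 2, however, refer to interviews with family members in general.

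**The concern.** A schedule decides what is collected, and no analysis plan can recover a time point that was never scheduled. If sites and the online data capture follow Table 1, one listed outcome, PVA change to six-month follow-up, will have no follow-up data. It bears on a substantive question: whether parents' confidence in supporting recovery lasts after treatment ends. Once a family's T4 assessment has passed, the value cannot be obtained. If the comparison is then dropped without comment, readers will see a prespecified outcome go unreported.

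The other two mismatches carry less weight. The CET sentence promises a mid-treatment comparison without mid-treatment data. The sibling text leaves it unclear whether the fourth role in the qualitative comparison will have any interviews to analyse.

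**Working it through.** No sample size, power or error-rate figure is involved, so the check sets what each analysis needs against what the schedule supplies.

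| Item | Needed by the analysis | Supplied by the schedule | Missing |
|---|---|---|---|
| PVA (Primary outcomes; Aim 1) | T1, T3, T4 | T1, weekly-column 2/4/6, T2, T3 | T4 |
| CET (Aim 1) | T1, T2, T3, T4 | T1, T3, T4 | T2 |
| CET (Primary outcomes) | T1, T3, T4 | T1, T3, T4 | none |
| CIA (same Aim 1 sentence as CET) | T1, T2, T3, T4 | T1, T2, T3, T4 | none |
| Interview roles (Aim 2) | young person, parent/guardian, sibling/other, therapist | young person, parent/guardian, therapist (Measures) | sibling/other, unless covered by family members |

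*Is the PVA gap real or a misaligned table?* In the same block, FAD, PEDE, PEDE-Q, parent RCADS and EQ-5D-5L are all marked at T4. PVA is the only repeated parent measure without a T4 mark. In the young person's block, CIA has its T2 mark where expected and CET does not. The neighbouring rows are aligned, so both gaps appear to be as the authors set them.

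*Could the mixed model supply PVA at T4?* Such a model can handle T4 values missing for some parents because others were observed. Here no parent is observed at T4, so the T4 mean is not identified. The only route is to extrapolate a time trend. Treatment runs 9 months and follow-up is 6 months later, so T4 falls at about 9 + 6 = 15 months. The extrapolation would cover 6 months after the last observation, in a period when treatment has stopped. That is not an estimate of observed change.

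*What survives?* PVA change from T1 to T3 has both its time points. So do both CET changes listed under Primary outcomes. A model can be fitted to CET without T2; only the stated T2 comparison lacks data.

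*Sibling interviews.* The sections for the young person, parents/guardians and therapist each describe a survey or questionnaire plus a semi-structured interview. The sibling section describes a survey alone, in line with the invitation list in Measures. On the other side, Aim 2 names siblings as an interview role, and family members in Secondary outcomes and in item (e) can include them. Table 1 gives siblings a T3 treatment-evaluation mark without saying whether it means survey or interview. The text supports both readings.

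**The case against.** The best counter-argument is that little is lost. PVA and CET are both collected repeatedly, and each lacks one time point. Aim 1 names %mBMI change as the primary outcome and introduces secondary analyses after it, so the effectiveness conclusion does not rest on PVA at T4. The PVA is described as a measure for parents taking part in FBT, so stopping it at the end of treatment may be deliberate, with the error lying in the text and not in the table. All of this stands. It limits the weight of the point and means either side may be corrected, but it does not remove the contradiction.

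A second argument is that a journal article condenses a fuller protocol. That would excuse an omission. Here the article prints both the schedule and the analyses, and they disagree. An analysis plan not shown could drop the comparison, but it could not supply the data.

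Three stronger readings are tempting and should be resisted:

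- A reader might infer that a primary outcome of the trial is lost, because PVA stands under the Primary outcomes heading. Aim 1 does not treat it as the primary outcome.
- A reader might infer that no sibling will be interviewed. Secondary outcomes, item (e) and the role list in Aim 2 point the other way, so this is a conflict between sections and not a demonstrated loss of data.
- A reader might add the CGAS, which is described under Measures but has no row in Table 1. No stated outcome or analysis uses it, so it is an editorial leftover and not part of this point.

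**Conclusion.** The point holds in a limited form. If Table 1 is followed, PVA change from T1 to T4 cannot be estimated: 0 of the planned 40 families would have a T4 value. That count simply restates the empty cell and assumes no collection outside the schedule. PVA change from T1 to T3 and %mBMI change are unaffected.

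The CET mismatch is minor. One time point in one analysis sentence has no data, and the listed CET outcomes are intact. The sibling item is an inconsistency that the authors must resolve; the documents do not show which version is intended.

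This is an internal inconsistency worth correcting before T4 assessments are complete. It does not threaten the trial's main effectiveness result.

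**What to change.** 1. **PVA.** Either add the seven-item PVA to the T4 column of the Parents/Guardians block in Table 1, or delete T4 for PVA from both Primary outcomes and Data analysis, Aim 1. The first costs one short questionnaire at an assessment parents already complete. The second costs only wording but gives up the follow-up result. The choice depends on whether parental self-efficacy after treatment is of interest, which the authors should state.
2. **CET.** Remove T2 for CET from the Aim 1 sentence, keeping it for CIA, or add CET at T2 in Table 1. The first is a wording change; the second adds one questionnaire at mid-treatment.
3. **Sibling interviews.** Reconcile Measures, the Siblings/other family members section, Secondary outcomes and Aim 2. Either state that siblings are invited to interview, or limit their part of the Aim 2 analysis to survey data and say who counts as family members. The first adds interviews and their analysis; the second is wording only.
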